**Fig. 1 Fig1:**
[figure not shown]
Flow of participants through the trial. *MT* manual therapy, *Ex* exercise

All outcome measures will be taken by staff of the hospital familiar with administering these assessments and blinded to a participant’s group allocation. Lung function measurements are measured in the sitting position and include FEV_1_ and FVC. Exercise capacity is assessed using the 6MWT where capacity is determined by the total distance walked on a flat surface (hospital hallway) in a period of 6 minutes. Quality of life (SGRQ) and anxiety and depression (HADS) scores are calculated using the standard procedures for these questionnaires. Frequency of exacerbations is gathered by direct questioning of a participant. Systemic inflammatory biomarkers are measured via blood sampling by the hospital’s pathology department from samples (10 mL) collected by a registered nurse who is blinded to a participant’s group allocation. The SPIRIT figure showing the respective time points for enrolment, interventions and assessments is provided in Fig. 2.

**Fig. 2 Fig2:**
[figure not shown]
SPIRIT figure showing time points for enrolment, interventions and assessments. *FEV*
_*1*_ Forced expiratory volume in the 1^st^ second, *FVC* Forced vital capacity, *SGRQ* St George’s Respiratory Questionnaire, *HAD* Hospital Anxiety and Depression (scale), *CRP* C-reactive protein

All MT is administered by chiropractors and/or osteopaths with more than 5 years of experience in the manual therapy protocol (MTP) used in this trial. This is the same MTP that was used in two previous trials on patients with COPD [22, 23]. It consists of a combination of soft tissue (ST) therapy and thoracic spinal manipulation (SM).

The ST component of the MTP consists of gentle effleurage and cross-fibre friction therapy applied to the muscles of the posterior chest wall including the intercostal, serratus posterior and anterior, rhomboid, trapezius, latissimus dorsi, erector spinae, quadratus lumborum and levator scapulae muscles. The SM component consists of two separate manipulations (Grade V mobilisation [24]). Each manipulation involves the delivery of a high-velocity low-amplitude (HVLA) posterior-to-anterior force directed towards the intervertebral, costovertebral and costotransverse joints. The first manipulation is administered at the level of the upper/middle thoracic spine, while the second is administered at the level of the middle/lower thoracic spine. All SM are administered as non-specific, multi-joint (group) manipulations. Administering SM in this way reduces the total number of manipulations required in a single session, as each manipulation has the potential to affect several thoracic vertebrae and their associated ribs simultaneously. An MT session lasts approximately 20 minutes and is administered just prior to exercise intervention in the MT + Ex Group.

### Consent process

The consent process followed in this trial will be the same for all participants. Potential participants will receive the Patient Information and Consent Form (PICF) explaining the trial’s processes and procedures, including consent to publish, and what is expected from them during the trial. Each participant will be given the opportunity to ask questions about their involvement in the trial and to have those questions answered by a researcher associated with the trial prior to providing consent. A trial-specific ID number will be used when gathering and recording all information about a participant. A list containing the contact details of all participants and their corresponding ID numbers will be kept separate from all other data. All paper copy forms will be stored in a locked filing cabinet in the hospital facility during the trial. Once the intervention phase of the trial has been completed (week 26), all data from these files will be transferred to a password-protected encrypted file and stored on the chief investigator’s university computer located in his locked university office. These files will be backed up on an external hard drive and stored in a locked filing cabinet in the university office of another investigator. The trial was approved by the South Eastern Sydney Local Health District - Human Research Ethics Committee (HREC): approval number 13/004.

### Sample size calculation

The sample size calculation was based on FVC. The minimum clinically important difference for FVC is 200 mL with the standard deviation obtained from previous studies [22, 23]. With a power of 0.8 (80%) and an alpha of 0.05, the minimum sample size per group is 92. Assuming a drop-out rate of 10%, the minimum cohort size would be 202 (two groups of 101).

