## Methods/design

### Study design

The trial is designed as a randomised controlled trial and fulfils the requirements of the Standard Protocol Items: Recommendations for Interventional Trials (SPIRIT) checklist [21] (Additional file 1). It will evaluate 202 participants randomly allocated to two equal groups. Participants in Group 1 (Ex) will undergo an exercise regime that has been modelled on an existing pulmonary rehabilitation program; participants in Group 2 (SM + Ex) will have MT which includes SMT administered to their thoracic spine and ribs just prior to performing the same exercise regime as Group 1. Participants will be recruited through direct referral from their respiratory specialist or general practitioner or through self-referral in response to public advertisements calling for volunteers for the trial. The trial is being conducted in the pulmonary rehabilitation department at Sutherland Hospital in Sydney, Australia.

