### Statistical analysis

Data will be reported as group means, standard deviations and 95% confidence intervals. Analysis will be performed as an analysis of covariance (ANCOVA) for differences between groups with baseline as a covariate. Standard errors will be calculated using a non-parametric bootstrap to allow for the different error variances for each group. A *p* value of < 0.05 has been set for statistical significance. For outcomes found to be statistically significant, the proportion of participants with a change greater than the minimum clinically important difference will be calculated for each outcome. The number needed to treat will be calculated using Bender’s method for confidence intervals. Missing data will be accounted for by using an intention-to-treat analysis with data from subjects lost to follow-up imputed using the multiple imputation method.

Two interim analyses are planned before the final analysis. They are mid-trial following the second blood test (week 24) and 6 weeks after completion of all interventions (week 32). The conduct of the trial will not be affected by the results of these interim analyses.

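### With the stated 10% drop-out, two groups of 101 leave about 91 per group, below the stated minimum of 92, so 202 is not the minimum cohort size

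*Protocol article*

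**What the plan says.** The section on sample size in the protocol article gives a short chain of figures:

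- Endpoint: "The sample size calculation was based on FVC".
- Difference to detect: "The minimum clinically important difference for FVC is 200 mL".
- Variability: "with the standard deviation obtained from previous studies", with no value printed.
- Error rates: "With a power of 0.8 (80%) and an alpha of 0.05". The text does not say whether alpha is one- or two-sided.
- Result before drop-out: "the minimum sample size per group is 92".
- Result after drop-out: "Assuming a drop-out rate of 10%, the minimum cohort size would be 202 (two groups of 101)".

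The Abstract repeats the total of 202, and so does the Study design section: "It will evaluate 202 participants randomly allocated to two equal groups". The formula for the drop-out allowance is not given. The Statistical analysis section plans an ANCOVA with baseline as covariate and an intention-to-treat analysis with "data from subjects lost to follow-up imputed using the multiple imputation method".

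**The concern.** A drop-out rate is ordinarily the share of those randomised who are later lost. An allowance for it should therefore leave the required number after that share is removed from the randomised total. Here the required number is 92 per group, the rate is 10%, and the number randomised is 101 per group. If 10% of 101 are lost, fewer than 92 remain, so the figure presented as a minimum does not deliver the minimum stated just before it.

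What is at stake is the correctness of the trial's headline sample size. The total of 202 appears in three places, and a reader will take it to secure 92 per group and 80% power at the stated drop-out. It falls slightly short of that.

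**Working it through.** **Inputs**, all from the Sample size calculation section: 92 per group (184 in total) required; drop-out 10%; 101 per group (202 in total) randomised; difference 200 mL; power 0.80; alpha 0.05. The 1:1 allocation is also in Study design. Assumptions needed for the power step only: a two-sided test, and a standard deviation solved back from n = 92.

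**1. Reproducing the printed figure.**
- 92 × 1.10 = 101.2, rounded down to 101.
- 184 × 1.10 = 202.4, rounded down to 202.

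Both printed numbers are matched exactly, so an allowance of n × (1 + d), rounded down, is the likely route. This is an inference from the match.

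**2. What remains after a 10% loss.**
- Per group: 101 × 0.90 = 90.9, against 92.
- In total: 202 × 0.90 = 181.8, against 184.

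In whole persons that is 90 or 91 per group, below 92 under either rounding.

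**3. What would be needed to keep 92.**
- n / (1 − d) = 92 / 0.90 = 102.2, so 103 per group and 206 in total.
- Check: 102 × 0.90 = 91.8 (too few); 103 × 0.90 = 92.7 (enough).
- If only the total is inflated: 184 / 0.90 = 204.4, so 205, which is not divisible into two equal groups.

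**4. The drop-out that 202 can absorb.**
- 1 − 92/101 = 0.089, so 8.9%.

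**5. The generous reading of 10%.** If 10% meant 10% of the 92 required rather than of those randomised, 101.2 per group would be needed. A minimum must be rounded up, giving 102 per group and 204 in total. The printed 101 misses this too, though only by the rounding.

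**6. Size in terms of power.** The standard deviation is not stated. With the normal approximation, n = 2(1.960 + 0.842)² SD² / 200², and n rounds up to 92 for whole-number SDs of 482 to 484 mL. Power at 90.9 per group is then:

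| SD (mL) | Power, normal approximation |
|---|---|
| 482 | 79.9% |
| 483 | 79.7% |
| 484 | 79.6% |

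If power is exactly 80% at n = 92 (SD 484.2 mL), power at 90.9 is 79.5%. A t-test calculation implies a slightly smaller SD for exactly 80% at 92 (481.6 mL) and also gives 79.5% at 90.9. The loss against 80% at the expected number retained is therefore about 0.1 to 0.5 percentage points. The lower end arises because 92 may itself have been rounded up. Steps 1 to 5 do not use the standard deviation at all.

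**The case against.** **The discrepancy is immaterial.** The shortfall is 1.1 participants per group, and four of 206 to randomise (2%). A round 10% planning assumption, for which the article gives no source, is far less certain than the gap between 8.9% and 10%. This stands as a statement about size, and it is why the point is minor. It does not make the printed figures consistent.

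**Multiple imputation keeps everyone in the analysis.** With seven measurement occasions, participants who leave part-way may still contribute information, so 90.9 is a count of those who complete. That softens the point. Imputation does not in general restore all the lost outcome information, however, and the protocol itself treats drop-out as costing sample size, because it inflates for it.

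**ANCOVA may more than make up the loss.** If the standard deviation taken from the earlier studies was a raw between-person one, adjusting for baseline multiplies it by √(1 − r²). At SD 484 and 90.9 per group, an assumed baseline–outcome correlation of 0.2 would bring power to about 81%, and 0.5 to just under 90%. If the standard deviation was already for change or residuals, this gain may not apply. The article does not say which it was, so whether actual power lies above or below 80% cannot be settled from it. This stands, and it rules out a stronger claim. It does not repair the step from 92 and 10% to 202.

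**A stronger reading.** A reader might infer that the trial is underpowered, or that the Discussion is wrong to describe its power as adequate. The article does not support that. The loss is a fraction of a percentage point, it rests on a standard deviation that is not printed, and baseline adjustment could outweigh it.

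**Conclusion.** The point holds as a minor arithmetic correction. As printed, 92 per group, 10% drop-out and a minimum of 202 cannot all be true: 202 randomised with 10% lost leaves about 91 per group. Nothing elsewhere in the article reconciles them.

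The count check rests only on printed numbers and the usual meaning of a drop-out rate. The power statement (at or marginally below 80%) is conditional on a two-sided test, on the standard deviation implied by 92 per group, and on an unadjusted comparison of those who complete. It should not be quoted as a precise figure. The use of multiplication by 1.10 is inferred. No estimate, test or conclusion of the trial is put in doubt.

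**What to change.** Correct the one sentence in the Sample size calculation section. Any of these makes it consistent:

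- Keep 202 and state that it preserves 92 per group only if drop-out is at most 8.9%.
- Keep 202 and 10%, and state that about 91 per group are then expected to have outcome data, with power at or marginally below 80%. Print the standard deviation and the sidedness if a power figure is given.
- Keep both 92 and 10%, and change the minimum to 206 (103 per group), with the total amended in the Abstract and Study design.

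The first two cost one sentence and no extra participants. The third means four more participants; the article reports recruitment as ongoing at submission. Given the size of the discrepancy, the first is sufficient.

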### Statistical analysis

Data will be reported as group means, standard deviations and 95% confidence intervals. Analysis will be performed as an analysis of covariance (ANCOVA) for differences between groups with baseline as a covariate. Standard errors will be calculated using a non-parametric bootstrap to allow for the different error variances for each group. A *p* value of < 0.05 has been set for statistical significance. For outcomes found to be statistically significant, the proportion of participants with a change greater than the minimum clinically important difference will be calculated for each outcome. The number needed to treat will be calculated using Bender’s method for confidence intervals. Missing data will be accounted for by using an intention-to-treat analysis with data from subjects lost to follow-up imputed using the multiple imputation method.

Two interim analyses are planned before the final analysis. They are mid-trial following the second blood test (week 24) and 6 weeks after completion of all interventions (week 32). The conduct of the trial will not be affected by the results of these interim analyses.

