**Methods/design:**

The study is a randomised controlled trial of 202 people with stable mild COPD. The cohort will be divided into two equal groups matched at baseline. The first group will receive a standardised exercise program. The second group will receive MT that includes SMT plus the same standardised exercise program. Exercise will be administered a total of 36 times over an 18-week period, while MT will be administered in conjunction with exercise a total of 15 times over a 6-week period. The primary outcome measure is lung function (forced expiratory volume in the 1^st^ second: FEV_1_ and forced vital capacity: FVC). The secondary outcome measures are the 6-minute walking test (6MWT), quality of life questionnaire (St George’s Respiratory Questionnaire: SGRQ), anxiety and depression levels (Hospital Anxiety and Depression Scale: HADS), frequency of exacerbations, chest wall expansion measurements (tape measurements) and systemic inflammatory biomarker levels. Outcome measurements will be taken by blinded assessors on seven occasions over a 48-week period. Adverse event data will also be gathered at the beginning of each intervention session.

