### Participant characteristics

The trial includes both males and females between the ages of 50 and 65 years of age with a forced expiratory volume in the 1^st^ second (FEV_1_)/forced vital capacity (FVC) ratio of < 0.7 and an FEV_1_% predicted of 60–80% (COPDX 2016: mild COPD). Participants will be excluded if they are currently smoking, cannot complete a 6-minute walking test (6MWT) unassisted, have a history of autoimmune disease or are contra-indicated to SMT. Inclusion and exclusion criteria are described in Table 1.

**Table 1 Tab1:** Inclusion and exclusion criteria for participation

Inclusion criteria	Exclusion criteria
• Male and female • 50–65 years • Mild COPD (60% ≤ FEV_1_% < 80%: COPDX) • Stable COPD (no exacerbations in preceding 6 months) • Non-smoking (for preceding 6 months) • Willingness to provide written consent • Willingness to participate in and comply with the study requirements	• Inability to complete 6-minute walking test unassisted • History of auto-immune disease, e.g. RA or SLE that may have altered systemic inflammatory biomarkers • Contra-indicated to thoracic spinal manipulation o Bone density (DEXA) scores below minimum levels (T score < –2.5 and/or Z score < –1) o Thoracic joint instability o Acute pain on thoracic joint range of motion testing o Advanced chest wall muscle wasting o High level of anxiety related to receiving thoracic spinal manipulation • Inability to understand English • Inability to provide informed consent, e.g. people with a cognitive impairment, an intellectual disability or a mental illness • Completed a PR program in the previous 12 months

*COPD* chronic obstructive pulmonary disease, *COPDX* the COPD-X Plan. Australian and New Zealand guidelines for the management of chronic obstructive pulmonary disease. Version 2.45. March 2016, *FEV*
_*1*_
*%* forced expiratory volume in the 1^st^ second percent predicted (age-matched), *RA* rheumatoid arthritis, *SLE* systemic lupus erythematosus, *DEXA* dual energy X-ray absorptiometry, *PR* pulmonary rehabilitation

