### Protocol description

Volunteers who meet the inclusion criteria will be given an information sheet and asked to provide written consent to participate in the trial. They will then undergo a physical screening examination for the presence of contra-indications to thoracic MT. After successfully passing this screening, they will be enrolled in the trial, given a trial-specific identification (ID) number and allocated to a group sequentially using a computer-generated random sequence list drawn up prior to the start of the trial by a member of the staff not involved in any other aspect of the trial. Baseline measurements for each participant are then taken. These include lung function assessment using spirometry, exercise capacity (6MWT), chest wall expansion (tape measure), quality of life (St George’s Respiratory Questionnaire: SGRQ), anxiety and depression levels (Hospital Anxiety and Depression Scale: HADS) and systemic inflammatory biomarker levels via blood sampling (C-reactive protein (CRP) and leukocyte count). The study protocol flow of participants is outlined in Fig. 1.

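### For exacerbation frequency the stated baseline adjustment is empty, leaving an unadjusted comparison of mean counts that does not model time at risk

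*Protocol article*

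**What the plan says.** The Statistical analysis section of the protocol article states one between-group model: "Analysis will be performed as an analysis of covariance (ANCOVA) for differences between groups with baseline as a covariate". Standard errors come from a non-parametric bootstrap, and values for people lost to follow-up are multiply imputed. The summaries are also common to everything: "Data will be reported as group means, standard deviations and 95% confidence intervals". No outcome is exempted.

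The Abstract (Methods/design) lists exacerbations among the secondary outcomes: "anxiety and depression levels (Hospital Anxiety and Depression Scale: HADS), frequency of exacerbations, chest wall expansion measurements (tape measurements) and systemic inflammatory biomarker levels". It also sets the follow-up: "Outcome measurements will be taken by blinded assessors on seven occasions over a 48-week period".

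Three other statements bear on what a baseline value for this outcome could be:

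- Table 1, inclusion criteria: "Stable COPD (no exacerbations in preceding 6 months".
- Protocol description, baseline measurements: the list runs from "These include lung function assessment using spirometry, exercise capacity (6MWT), chest wall expansion (tape measure), quality of life" to "systemic inflammatory biomarker levels via blood sampling (C-reactive protein (CRP) and leukocyte count". It covers the other outcomes but does not name exacerbations.
- Protocol description, after Fig. 1: "Frequency of exacerbations is gathered by direct questioning of a participant". No look-back period is given.

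**The concern.** A baseline covariate helps only if it varies between participants. Eligibility fixes the recent exacerbation history at zero for everyone, so the rule written for spirometry, walking distance and questionnaire scores has nothing to adjust for here.

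What is left is a difference in mean counts. That is an awkward analysis for an event count over 48 weeks. People who leave early have a known time at risk, which the model does not use, and a mean with a standard deviation describes a count with many zeros poorly. At stake are the adjustment and the clarity of the result for one secondary outcome. If the mismatch is found only after data by arm have been seen, the choice of a replacement model becomes post hoc. The article plans interim analyses at weeks 24 and 32.

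**Working it through.** The article gives no figure for exacerbations (no expected rate, effect or power), so there is nothing of its own to reproduce. The sample size rests on FVC and does not bear on this point.

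**1. Design matrix.** Inputs: 202 participants, 101 per arm (Sample size calculation); baseline count b = 0 for everyone over the 6-month window (Table 1). The model is y = β0 + β1·arm + β2·b + error. The columns are an intercept, an arm indicator and b, so X′X is:

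- row 1: 202, 101, 0
- row 2: 101, 101, 0
- row 3: 0, 0, 0

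The upper 2 × 2 block has determinant 202 × 101 − 101 × 101 = 10,201, which is not zero. The third row and column are zero. The rank is 2 of 3, X′X is singular, and β2 cannot be estimated. A numerical check of the 202 × 3 matrix also gave rank 2. The bootstrap does not change this, because every resample has the same constant column.

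**2. What remains.** With b removed, the least-squares estimate of β1 is the difference between the two arm means. In one illustrative simulated data set (Poisson counts, assumed means 0.6 and 0.4, 101 per arm), the arm effect was −0.178 with an ordinary least-squares standard error of 0.093. Both were the same with the zero column present (minimum-norm fit) or removed, and −0.178 equalled the raw difference in means.

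**3. Time at risk.** Planned drop-out is 10%: 0.10 × 202 = 20.2 people. The gap between the enrolled and required numbers is 202 − 2 × 92 = 18. So about 18 to 20 participants may have incomplete follow-up. A difference in mean counts has no term for observed time. The article imputes data for those lost and does not say how partly observed counts enter.

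**4. Mean and standard deviation as a summary.** Under the same assumed Poisson means, the share with no event would be exp(−0.6) = 55% and exp(−0.4) = 67%. The standard deviations would be √0.6 = 0.77 and √0.4 = 0.63, each larger than its mean. These rates are assumptions; the article gives none.

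**5. Could another baseline vary?** The criterion fixes only the last 6 months. If a 12-month history were taken, events in the earlier 6 months could differ between people. With an assumed constant Poisson rate r per year, the share with at least one is 1 − exp(−r/2):

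| r per year | share with at least one event |
|---|---|
| 0.3 | 14% |
| 0.6 | 26% |
| 1.0 | 39% |
| 1.5 | 53% |

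Such a covariate would be usable, but the article describes no such look-back.

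**The case against.** The strongest reply is that this is the short statistics section of a journal article. It never says in terms that the ANCOVA covers every outcome, and a separate count model for a secondary outcome may stand in an analysis plan that is not at hand. That is fair as to what may exist elsewhere. It does not dispose of the point, because the article did not leave the model open: it fixed one rule without exception, and its own eligibility criterion empties that rule for an outcome it names.

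Three stronger readings are tempting, and the document does not support them.

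- A reader might infer that the analysis cannot be run. Software drops a constant column, and the arm effect remains. Under randomisation, a difference in mean counts with bootstrap standard errors is a valid comparison, if an inefficient one. No bias has been shown.
- A reader might infer that no baseline exacerbation history is taken. The baseline list is introduced as inclusive rather than exhaustive, the schedule in Fig. 2 is not shown, and a longer look-back could vary between people. The omission is well supported, not certain.
- A reader might infer that the same rule is also wrong for CRP. Baseline CRP is listed, so the covariate exists. The article gives no CRP distribution, and any gain from a log scale depends on assumed skewness, correlation and effect. In simulation under such assumptions, the raw-scale ANCOVA kept its type I error (4.7% to 5.0%) and was only less efficient.

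It also stands that multiple imputation is a stated way of handling loss to follow-up. The loss from using it here, rather than observed time at risk, has not been quantified.

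**Conclusion.** The point holds in a limited form. On the only baseline window described, the covariate for exacerbations is zero for everyone, so the stated adjustment does nothing. The analysis becomes an unadjusted difference in mean counts with no term for time at risk. This worth correcting but not critical: it affects one secondary outcome, the arm effect remains estimable, and the primary FEV1 and FVC analysis and the sample size are unaffected.

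The conclusion rests on two readings: that the single model applies to exacerbations, since nothing exempts them, and that baseline means the 6-month history in the eligibility criterion. If a longer history is recorded and used as the covariate, the rank problem goes, but the points about time at risk and the summary of counts remain. The size is given by the rank result (2 of 3) and the 18 to 20 people with possibly incomplete follow-up. No loss of power or bias is claimed.

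**What to change.** In the Statistical analysis section, or in the analysis plan before data by arm are examined:

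- Exempt exacerbation frequency from the ANCOVA rule and from the summary by mean and standard deviation.
- Analyse the number of exacerbations by negative binomial regression with log(time at risk) as offset. Use arm plus a baseline variable already collected, for example baseline FEV1 % predicted, as covariates.
- Report the rate ratio with its 95% confidence interval, and events and person-time by arm.
- Use each participant's observed follow-up, partial or complete, without imputing counts.
- Keep the stated ANCOVA for the other outcomes.

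The cost is wording, a second model and an effect measure on the ratio scale. No extra participants or assessments are needed. Time at risk can be taken from the assessment visits, provided that the date of the last questioning is recorded. Because eligibility confines FEV1 % predicted to 60–80%, the precision gained from that covariate may be small; the main gain is the proper use of exposure time.

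### Responder proportions, and by implication the NNT, are calculated only for outcomes that reach p < 0.05, so the NNTs that get reported are on average too favourable

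*Protocol article*

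**What the plan says.** All the relevant text is in two sections of the protocol article.

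- **Statistical analysis, the condition.** "For outcomes found to be statistically significant, the proportion of participants with a change greater than the minimum clinically important difference will be calculated". The threshold is the general one: a p value below "0.05 has been set for statistical significance".
- **Statistical analysis, the NNT.** "The number needed to treat will be calculated using Bender’s method for confidence intervals". This sentence follows directly on the conditional one and does not repeat the condition.
- **Statistical analysis, the test behind the filter.** "Analysis will be performed as an analysis of covariance (ANCOVA) for differences between groups with baseline as a covariate".
- **Statistical analysis, what is reported without condition.** "Data will be reported as group means, standard deviations and 95% confidence intervals".
- **Sample size calculation.** "The minimum clinically important difference for FVC is 200 mL", "with the standard deviation obtained from previous studies". The size of that SD is not printed. Power is 80%, alpha 0.05, and the result is 92 per group before drop-out.

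**The concern.** An estimate that is shown only when it passes a significance test is, on average, larger than the effect it estimates, because the low draws are removed and the high draws are kept. The responder difference comes from the same participants as the mean difference, so it inherits the exaggeration. The NNT, its reciprocal, then comes out too small. Nothing in the section corrects for this.

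The second consequence is uneven reporting. An outcome that passes gets a responder proportion in each arm and an NNT; an outcome that just misses gets neither. A table built this way shows the clinical translation only for the favourable part of the results.

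This matters because the Discussion presents the trial as evidence on whether manual therapy adds to pulmonary rehabilitation, and an NNT is easily carried over into practice. The sample size was set on FVC alone. Power for the other outcomes is not stated, and the filter distorts most where power is low.

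**Working it through.** **Inputs from the article.** Minimum clinically important difference (MCID) for FVC 200 mL; 92 per group; alpha 0.05; power 80%; responder = change above the MCID; filter = p < 0.05.

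**Assumptions.** Two-sided test; normally distributed changes; mean change of zero in the exercise-only arm; 92 analysed per arm; a t-test on change standing in for the ANCOVA; one time point. FVC is used because it is the only outcome whose MCID is printed.

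**Step 1: the SD.** From n = 2(1.96 + 0.8416)² SD² / 200² with n = 92:

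SD = 200 × √(92/2) / 2.8016 = 200 × 6.782 / 2.8016 ≈ 484 mL.

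Putting 484 mL back in returns 92, but that is circular: the article's figure cannot be reproduced independently. I therefore take 484 mL as an assumed SD of change and use 300 mL as a sensitivity value, since adjustment for baseline could make the residual SD smaller.

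**Step 2: what the filter lets through.** Standard error of the difference = 484 × √(2/92) ≈ 71.4 mL. Significance needs an observed difference of about 1.96 × 71.4 ≈ 140 mL. If the true effect is 100 mL, every significant favourable result therefore overshoots it. The mean of the estimates that pass is, in closed form, δ + SE × φ(a)/(1 − Φ(a)), with a = (140 − δ)/SE:

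- δ = 200: a = −0.84; 200 + 71.4 × 0.280/0.800 ≈ 225 mL.
- δ = 100: a = 0.56; 100 + 71.4 × 0.341/0.288 ≈ 184 mL.

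**Step 3: true NNT.** Responder share = P(change > 200 mL). In the control arm, P(Z > 200/484) = 0.3397.

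- δ = 200: 0.5000 − 0.3397 = 0.1603, NNT 6.2.
- δ = 150: 0.4589 − 0.3397 = 0.1192, NNT 8.4.
- δ = 100: 0.4182 − 0.3397 = 0.0785, NNT 12.7.

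**Step 4: NNT after the filter.** Trials were simulated participant by participant (at least 20,000 per scenario). The filtered NNT is the reciprocal of the mean risk difference among significant trials.

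| SD (mL) | True effect (mL) | Trials with p < 0.05 | Mean difference in those trials (mL) | True NNT | Filtered NNT |
|---|---|---|---|---|---|
| 484 | 50 | 11% | 162 | 25.9 | 8.0 |
| 484 | 100 | 29% | 184 | 12.7 | 6.9 |
| 484 | 150 | 55% | 201 | 8.4 | 6.3 |
| 484 | 200 (planned) | 80% | 225 | 6.2 | 5.5 |
| 484 | 250 | 94% | 259 | 5.0 | 4.8 |
| 484 | 300 | 99% | 303 | 4.1 | 4.1 |
| 300 | 100 | 61% | 127 | 8.6 | 6.7 |
| 300 | 200 (planned) | 99% | 201 | 4.0 | 4.0 |

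Repeat runs differ only in the last digit (5.5 to 5.6 at the planned effect). Without the filter, the mean risk difference equals the true one in every row, apart from simulation noise.

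**Step 5: interval coverage after the filter.** This used a score-based interval for the risk difference, taken here as the basis of the method the article names, with SD 484 mL. Coverage is about 80% at 50 mL, 92% at 100 mL and 96–97% from 150 to 250 mL.

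**The case against.** The strongest reply is that the rule is disclosed, changes no primary test, estimate or sample size, and does little harm where the trial was planned: at 200 mL the shift is about 0.7 NNT units (6.2 − 5.5), and from 250 mL upwards it almost vanishes. The largest distortions need a true effect of half the MCID or less, and all of them rest on an SD that the article does not print. That stands, and it limits the size of the point. It does not remove it: the true effect is unknown, and power for outcomes other than FVC is not stated. Nor is this a detail left to an analysis plan, because the article states the rule outright.

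Four stronger readings are tempting and are not supported.

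- *The article says that the NNT is restricted to significant outcomes.* It does not say so. The condition is inferred from the order of the sentences and from the NNT's need for the responder proportions.
- *The nominal 95% interval for the NNT fails in general.* Step 5 shows coverage at or above nominal near the planned effect; it falls clearly below 95% only for small true effects.
- *Readers cannot tell whether a benefit or harm was excluded for a non-significant outcome.* They can, on the outcome's own scale, because means and 95% confidence intervals are promised without condition. Only the responder translation is missing.
- *The NNT appears only when chance has favoured it.* If the true effect is 200 mL, about 80% of trials pass the filter, mostly because the effect is real.

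**Conclusion.** The point holds as a bias in which responder proportions and NNTs get reported, and as missing responder figures for outcomes that miss p < 0.05. For FVC the bias is modest at the design effect: the mean difference is inflated by about 12% (225/200), which gives the NNT shift shown above. It grows as the true effect shrinks, so that at 100 mL the reported NNT is little more than half the true one (6.9/12.7 ≈ 0.54). With an SD of 300 mL it is absent at the design effect and moderate at 100 mL.

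These sizes rest on the back-solved SD, on normal changes with no mean change in the control arm, and on reading the NNT as conditional. The direction of the bias does not depend on the SD; its size does. The main between-group comparison is not touched. This is a cheap and worthwhile improvement to the plan, not a threat to the trial's main conclusion.

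**What to change.** In the Statistical analysis section, replace the opening clause of the responder sentence (up to its first comma) with: *For FVC and FEV1, and for each secondary outcome with a pre-specified MCID, regardless of statistical significance*.

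Then state that for each of these outcomes the report will give:

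- the responder proportion in both arms;
- the risk difference with its 95% confidence interval, combined over the imputations;
- the NNT with its interval by the method already named, including intervals that pass through infinity when the risk-difference interval contains zero.

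The cost is one reworded sentence and a few extra table rows; no new data are needed. The drawback is that NNT intervals for non-significant outcomes are harder to read. Printing the risk difference beside them helps.
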